## Abstract

**Background:**

Palliative care aims to contribute to pain relief, improvement with regard to symptoms and enhancement of health-related quality of life (HRQoL) of patients with chronic conditions. Most of the palliative care protocols, programmes and units are predominantly focused on patients with cancer and their specific needs. Patients with non-cancer chronic conditions may also have significantly impaired HRQoL and poor survival, but do not yet receive appropriate and holistic care. The traditional focus of palliative care has been at the end-of-life stages instead of the relatively early phases of serious chronic conditions. The ‘Patient-centred pathways of early palliative care, supportive ecosystems and appraisal standard’ (InAdvance) project implements and evaluates early palliative care in the daily clinical routine addressing patients with complex chronic conditions in the evolution towards advanced stages. The objective of the current study is to evaluate the acceptability, feasibility, effectiveness and cost-effectiveness of this novel model of palliative care in the relatively early phases in patients with chronic conditions.

**Methods:**

In this study, a single blind randomised controlled trial design will be employed. A total of 320 participants (80 in each study site and 4 sites in total) will be randomised on a 1:1 basis to the Palliative Care Needs Assessment (PCNA) arm or the Care-as-Usual arm. This study includes a formative evaluation approach as well as a cost-effectiveness analysis with a within-trial horizon. Study outcomes will be assessed at baseline, 6 weeks, 6 months, 12 months and 18 months after the implementation of the interventions. Study outcomes include HRQoL, intensity of symptoms, functional status, emotional distress, caregiving burden, perceived quality of care, adherence to treatment, feasibility, acceptability, and appropriateness of the intervention, intervention costs, other healthcare costs and informal care costs.

**Discussion:**

The InAdvance project will evaluate the effect of the implementation of the PCNA intervention on the target population in terms of effectiveness and cost-effectiveness in four European settings. The evidence of the project will provide step-wise guidance to contribute an increased evidence base for policy recommendations and clinical guidelines, in an effort to augment the supportive ecosystem for palliative care.

**Trial registration:**

ISRCTN, ISRCTN24825698. Registered 17/12/2020.

## Background

Population ageing is a long-term trend in Europe which began several decades ago [1]. In 2020, more than one fifth (20.6%) of the European Union (EU) population was aged 65 and over [2]. Moreover, the share of those aged 80 years or above is projected to more than double between 2016 and 2080 in the EU, from 5.4 to 12.7% [2].

With the predicted demographic shift, the prevalence of multi-morbidity, defined as the co-occurrence of two or more long-term conditions, will rise [3]. The prevalence of multi-morbidity among older persons (> 60 years) ranges from 55 to 98% worldwide [4]. For example, a study in Scotland reported that 65% of people aged 65–84 years and 82% of people aged 85 years and over are affected by chronic conditions and multi-morbidity [5]. The impact of chronic conditions and multi-morbidity may include impaired physical function, dependence, poor health-related quality of life (HRQoL), high care costs and decreased survival [6–8]. Palliative care is considered to be an appropriate way for pain relief, improvement of symptoms experience and well-being and enhancement of HRQoL of patients with chronic conditions. According to the World Health Organization (WHO), palliative care aims to improve the HRQoL of patients and their families who are facing the problems associated with life-threatening illnesses [9]. Palliative care prevents and relieves suffering by means of early identification, appropriate assessment and treatment of pain and other problems, whether physical, psychological, social or spiritual [9].

However, despite the growth in needs of palliative care services, it is estimated that only about 14% of people in need of palliative care are currently receiving it worldwide [10]. Most of the palliative care protocols, programmes and units are more focused on patients with cancer and their specific requirements and needs [11]. Patients with non-cancer chronic conditions may also have significantly impaired HRQoL and poor survival, but relatively often do not receive holistic and appropriate care according to their needs when compared to oncological patients [12, 13]. Furthermore, the core focus of palliative care providing relief from pain, physical symptoms, and psychosocial distress is at the end-of-life stages [14, 15]. As affirmed by the WHO, patients with chronic conditions may also benefit from palliative care actions in the early phases of their condition in conjunction with the specific life-prolonging treatments [16].

In addition, it is recognized that a relatively large share of healthcare resources is spent on the end-of-life care [17]. It is estimated that in the USA 25% of health-care expenditure is provided on patients’ last year of life [18]. Another study reported that in UK relatively 20% of hospital bed days are taken up by palliative care services [19]. However, the evidence base of cost-effectiveness evaluation to palliative care remains small [20–24]. One literature review reported that palliative care services mostly cost less relative to comparator groups (i.e. standard hospital setting, acute care services), and in most cases, the difference in cost is statistically significant [17]. More evidence on cost-effectiveness evaluation of palliative care is needed and can be served as drafting policy recommendations and clinical guidelines.

*The Patient-centred pathways of early palliative care, supportive ecosystems and appraisal standard* (InAdvance) project was set up to address the Horizon 2020 Call: SC1-BHC-23-2018 – ‘Novel patient-centred approaches for survivorship, palliation and/or end-of-life care’. The InAdvance project integrates early palliative care into daily clinical routine addressing patients with complex chronic conditions in evolution towards advanced stages.

## Aims and objectives

Within the InAdvance project at four locations a randomized trial will be performed lasting 18 months after the first intervention. In Valencia (Spain), Amadora (Portugal), Thessaloniki (Greece) and Highlands (UK) a novel model of palliative care will be implemented by integrating personalized pathways for palliative care that starts at an early stage of complex chronic conditions for older people (≥60 years old). The objective of our study is to evaluate acceptability, feasibility, effectiveness and cost-effectiveness of the novel model of palliative care in patients with chronic conditions.

In terms of effectiveness, self-reported outcome measures will be assessed with regard to both patients and informal caregivers/relatives to analyze the impact of the intervention on their wellbeing. The cost-effectiveness evaluation will assess whether there is ‘value for money’ and cost savings derived from the intervention. Finally, the implementation of the interventions process will be assessed at several times with the involvement of key healthcare professionals to identify facilitators and barriers of the implementation of the interventions.

We hypothesize that patients will have improved or maintained HRQoL and alleviated symptoms, and that multifaceted, complex needs including psychological, emotional and spiritual needs will be addressed. Informal caregivers/relatives will have improved or maintained HRQoL, increased social support, caring and coping skills and decreased caregiving burden. From the cost-effectiveness evaluation, we hypothesize that patients will have more efficient use of health care resources and contribute to a reduction of unnecessary costs.

## Methods/design

According to the needs identified and clinical pathways of each site, an intervention process was proposed based on the Consolidated Standards of Reporting Trials (CONSORT) flow diagram [25] aiming to: 1) identify patients who are at the advanced stage of their diseases, 2) assess potential palliative care needs of patients and their caregivers, and 3) define clinical pathways to address the identified needs. The NAT: PD (Needs Assessment Tool: Progressive Disease) [26] will be used to assess the needs of patients and their informal caregivers/relatives. The NAT: PD is a one-page assessment tool that consists of 21 items divided into four sections: 1) priority referral for further assessment; 2) patient wellbeing; 3) ability of caregiver or family to care for the patient; and 4) caregiver wellbeing. The level of concern is scored for each item as none, some or severe. The NAT: PD is developed to be used in both generalist and specialist settings that can facilitate decision-making on palliative care referrals to ensure that the identified needs can be better managed with appropriate services and support. The NAT: PD will be delivered either face-to-face or remotely via telephone or video, taking into consideration patient’s preferences and/or ability to visit the healthcare facility or respecting social distancing protocols established by national/regional health authorities under the current COVID-19 pandemic. The processing of personal data will be ensured in accordance with national and European regulations.

### Study design

The study has two stages. In stage one, a single blind randomised controlled trial will be conducted. Patients will be randomly assigned to two arms – the ‘Palliative Care Needs Assessment (PCNA)’ arm and the ‘Care-as-Usual’ arm. Primary intervention using the NAT:PD with repeated measures of the variables will be carried out in the PCNA arm. In stage two, patients and their informal caregivers/relatives assigened to the PCNA arm will benefit from a range of supportive programmes. These feasibility pilots in stage two will be adapted to the particularity of each clinical site. In Stage Two, in the ‘Care-as-Usual’ arm, the ‘usual care’ will be continued. The trial is registered at Cochrane Library: ISRCTN24825698.

The evaluation study of the InAdvance project includes a formative evaluation approach, which provides information regarding feasibility at real-time implementation (Fig. 1). After patients’ recruitment in the study, baseline data (T0) will be collected. Three intermediate evaluations will be performed at week 6 (T1), month 6 (T2) and month 12 (T3) after the implementation of the intervention. A final evaluation will be performed on month 18 (T4).

**Fig. 1 Fig1:**
[figure not shown]
Trial outcome evaluation schedule

### Study setting

The InAdvance intervention is a population-base prospective cohort study conducted in four settings. At the locations in Spain patients with multi-morbidity will be included. At the location in Greece patients with respiratory disease, patients with heart failure and patients with frailty will be included. At the location in Portugal and the UK patients with multi-morbidity or severe chronic obstructive pulmonary disease (COPD) will be included.

### Eligibility criteria and recruitment

Men and women of at least 60 years of age diagnosed with complex chronic conditions with a potential progressive course are eligible for the study, as well as their caregivers. A detailed description of the inclusion and exclusion criteria is shown in Table 1.

**Table 1 Tab1:** Inclusion and exclusion criteria related to patients for the needs assessment trail

Inclusion criteria	Exclusion criteria
• Participants with capacity to provide informed consent	• Individuals unable to provide written informed consent
• **Spanish, Portuguese and Greek sites:** No more than mild cognitive decline (≥18 points) on the Mini Mental State Examination (MMSE) [27] or up to 4 errors on the Pfeiffer Test [28] **UK site:** If the participant’s clinical record includes documented evidence of cognitive decline, participants should demonstrate no more than mild cognitive decline at screening (must score ≥ 18 points on MMSE)	• **Spanish, Portuguese and Greek sites:** Older adults diagnosed with cancer **UK site:** Older adults diagnosed with active cancer (excluding basal cell carcinoma and squamous cell carcinoma of the skin)
• Males and females	• Individuals currently enrolled on any other research which might interfere with the results and the procedure of the study
• Participants aged 60 years or older at the time of randomisation	• Individuals under the age of 60 years
• **UK, Portuguese and Greek sites:** Participants that have a clinical diagnosis of severe COPD or severe respiratory illness OR **UK site:** Participants with at least two co-occurrent chronic conditions (multi-morbidity), at least one of them being in a severe stage as determined by the patient’s clinical care team OR **Spanish and Portuguese sites:** Participants with at least two co-occurrent chronic conditions (multi-morbidity), at least one of them in a severe stage according to the specific criteria of severity and progression of disease of the NECPAL tool [29] OR **Greek site:** Participants that have a clinical diagnosis or severe respiratory illness and multi-morbidities (participants with severe heart failure, diabetes, lipidemia, hypothyroidism, or arthritis)	• Individuals who, in the opinion of the research team, may face physical or psychological risk/harm due to the invite participation or the enrolment on the study (i.e. subjects that are not aware of the severe prognosis, unstable clinical conditions)
• **Portuguese and Greek sites:** Owning a Smartphone and the ability to use it (or an informal care giver having the ability to use it)	
• **Spanish, Portuguese and Greek sites:** No previous referral to specialist Palliative Care **UK site:** No referral to specialist Palliative Care in the 2 years prior to randomisation	
• Be aware of their diagnosis and prognosis	
• Willingness to participate in the study	
• Not currently enrolled in other research studies	

### Sample size considerations

Assuming a statistical power of 95% and an effect size of 0.20 regarding continuous outcome measures between intervention and control group with an alpha risk of 0.05, the sample size is estimated to be 320 participants; that is 80 at each of the four sites with 40 participants in the intervention group and 40 in the control group. In the study, for each patient participating in the study, it is expected to include one informal caregiver (e.g. a family member) who provides informed consent to join the study. Furthermore, for the formative evaluation, 10–15 health care professionals will be recruited to participate in the study at each study site.

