### Data management and statistical analysis

The University of Valencia (UVEG) and the Erasmus Medical Center (Erasmus MC) are responsible for the analysis and reporting. UVEG, Erasmus MC and together with all clinical sites are responsible for the data manegement. All data will be gathered through the CASTOR eCRF system, which will be made available to the consortium.

Descriptive statistics will be carried out to summarize characteristics of participants in each clinical site and in the total study population. Tests for normal distribution of the continuous outcome measures will be performed using the Kolmogorov–Smirnov test. The outcome measures will be compared within each group (intervention group and control group) at different measurement times (i.e. T0-T1; T1-T2; T2-T3; T3-T4; T1-T4; T0-T4, etc.). A multilevel modelling approach will be used to examine differences in the outcome measures between the intervention and control group, taking into account the clustering effects at the clinical site level. The relationship between the outcome measures and independent variables will be assessed using Pearson correlation (for continuous variables) and Pearson Chi-square test (for categorical variables). Comparison between the intervention group and the control group at each evaluation moment will be conducted by including an interaction between the treatment groups and time in the multilevel model.

The cost-effectiveness analysis will be conducted from a societal perspective and on a within-trial horizon. The incremental cost-effectiveness ratio (ICER) will be calculated and the degree of uncertainty for costs and effectiveness and the cost-effectiveness ratio will be examined on the ICER by using non parametric bootstrapping. In addition, an acceptability curve will be generated to indicate the probability that the intervention has lower incremental costs per quality adjusted life year (QALY) gained than various thresholds for the maximum willingness to pay for an extra QALY.

In all cases, *p*-values < 0.05 will be considered statistically significant. All analyses will be carried out using the statistical package SPSS v26 or similar statistic software packages.

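### The sample size section gives 95% power for an effect size of 0.20 without naming the metric; as a standardised mean difference, 320 participants do not deliver it, and the readings that yield 320 mean about 0.40 SD

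*Protocol article*

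**What the plan says.** The section on sample size considerations in the protocol article bases the trial's size on one sentence. It begins "Assuming a statistical power of 95% and an effect size of 0.20 regarding continuous outcome measures between intervention and control group", continues "with an alpha risk of 0.05", and concludes that "the sample size is estimated to be 320 participants; that is 80 at each of the four sites", split 40 and 40 between the arms at each site. The Abstract repeats the total and the allocation: "A total of 320 participants (80 in each study site and 4 sites in total) will be randomised on a 1:1 basis".

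The sentence names no effect-size metric, test, sidedness, outcome, standard deviation or correlation. The section on data management and statistical analysis plans a multilevel model that allows for site, with a group-by-time interaction for the comparison at each evaluation, and says that p-"values < 0.05 will be considered statistically significant". The sample size sentence is not tied to that model.

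**The concern.** An effect size for a continuous outcome compared between two groups is ordinarily a standardised mean difference (Cohen's d). Read so, the sentence says that the trial is very likely to find a difference of one fifth of a standard deviation. A two-arm trial of 320 is far too small for that in a simple comparison, so either the power does not match the effect size or the effect size is on another scale and is unlabelled.

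At stake is what a null result can exclude. A reader who takes the sentence at face value would think that a non-significant difference makes a 0.20 SD benefit unlikely. If the trial was in fact sized for about 0.40 SD, that inference fails.

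**Working it through.** **Inputs.** From the sample size section: power 0.95, alpha 0.05, effect size 0.20, total 320, and 4 sites × 40 = 160 per arm. From the Abstract: 1:1 allocation. Not stated, so assumed: two-sided testing (one-sided also tried) and no covariate adjustment. Normal quantiles: 1.960 (two-sided 0.05), 1.645 (95% power, and one-sided 0.05), 0.842 (80% power).

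**Step 1. Can 320 be reproduced?**

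- *0.20 as Cohen's f, two equal groups.* Then d = 2f = 0.40. Per arm, n = 2(1.960 + 1.645)²/d² = 2 × 12.996/0.16 = 162.4, so 163, or 326 in total. The exact F test gives 327 in total, and power at 320 is 94.6%. This matches closely.
- *0.20 as a correlation.* N = [(1.960 + 1.645)/atanh(0.20)]² + 3 = (3.605/0.2027)² + 3 = 319.2. This also matches. For two equal groups, r = 0.20 corresponds to d = 2r/√(1 − r²) = 0.40/0.980 = 0.41.
- *0.20 as a standardised mean difference.* n = 2 × 12.996/0.04 = 649.8, so 650 per arm. The exact t-test needs 651 per arm, or 1,302 in total, about four times 320. One-sided, it is 542 per arm, or 1,084. Neither matches.

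A paired or one-sample test of a standardised change of 0.20 also needs 327 people. That is not a comparison between two arms, which is what the sentence describes.

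**Step 2. Power at 160 per arm if 0.20 is in SD units.** The standardised signal is d√(n/2) = 0.20 × √80 = 1.789.

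- Two-sided: Φ(1.789 − 1.960) = Φ(−0.171) = 0.432; exact t-test 0.430.
- One-sided: Φ(1.789 − 1.645) = Φ(0.144) = 0.557.

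**Step 3. Detectable difference at 160 per arm, two-sided.**

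- 95% power: (1.960 + 1.645)/√80 = 3.605/8.944 = 0.403; exact 0.404.
- 80% power: (1.960 + 0.842)/8.944 = 0.313; exact 0.314.

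**Step 4. Could the planned model rescue 0.20 SD?** To reach 95% power, the outcome variance would have to fall to 320/(2 × 650.7) = 0.246 of its raw value. The protocol gives no correlation ρ, so the values below are assumptions with complete data.

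- Baseline adjustment at one follow-up leaves a variance of 1 − ρ². Power for 0.20 SD is 54% at ρ = 0.5 and 71% at ρ = 0.7. Reaching 95% needs ρ = √(1 − 0.246) = 0.87.
- The baseline-adjusted mean of four follow-ups leaves (1 + 3ρ)/4 − ρ². This is 0.375 at ρ = 0.5 (power 83%), 0.285 at 0.7 (92%) and 0.210 at 0.8 (97%).

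**Step 5. What a null result would leave open.** The half-width of an unadjusted 95% confidence interval is about 1.960 × √(2/160) = 0.219 SD. Even an estimate of exactly zero would not exclude 0.20 SD.

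**The case against.** The strongest reply is that the sentence is not an arithmetic error at all. It never says that 0.20 is in SD units, and 320 follows closely from Cohen's f or from a correlation, both of them standard inputs to sample size software. This stands, and it rules out a flat statement that the 95% is wrong. It does not clear the sentence. Neither metric is named, the wording describes a difference between groups, and both metrics mean about 0.40 SD.

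A reader might also infer that the trial as planned has 43% power for 0.20 SD. The documents do not support that. The 43% belongs to an unadjusted t-test at one time point, whereas the plan is a multilevel model over repeated measures. It compares the arms at each evaluation, but an overall contrast is not excluded. With an averaged, baseline-adjusted contrast and high enough correlations, power for 0.20 SD could be far higher. No such contrast or correlation is cited in support of the figure, so the stated power cannot be credited to it.

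Two further inferences should be resisted. One is that the calculation wrongly ignores loss to follow-up: the sentence is silent on this, and silence in a condensed article is not an error. The other is that a null result will be reported as evidence against a small benefit: nothing in the article says how a null result will be presented.

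**Conclusion.** The concern holds conditionally. If 0.20 is a standardised mean difference, as the wording ordinarily implies, the stated power and the sample size do not fit each other: about 43% rather than 95% in an unadjusted two-sided comparison, with sidedness making too little difference to matter. If 0.20 is Cohen's f or a correlation, the calculation is sound to within a few participants, but its target is about 0.40 SD and the sentence conceals that. Either way the printed statement misleads on what the trial can detect by a factor of about two at 95% power.

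This rests on 160 per arm with complete data, alpha 0.05 two-sided and no variance reduction from baseline or repeated measures. It is a fault in the published figure and does not show that 320 is too few for the trial's purpose.

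**What to change.** In the sample size section, name the effect-size metric, the test and the sidedness, and give the target in SD units. If Cohen's f or a correlation was meant, wording such as this would do:

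> 320 participants (160 per arm) give about 95% power for a standardised mean difference of about 0.40, and 80% for about 0.31, in an unadjusted two-sided comparison at alpha 0.05.

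If 0.20 SD was the intended target, correct the power to about 43% for the unadjusted comparison, or give the power under the planned multilevel model together with the contrast and the correlations assumed.

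In either case, add that non-significant results will be interpreted through their confidence intervals and not taken to exclude a 0.20 SD effect.

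The cost is one paragraph of wording. Enrolment, allocation and analysis stay as they are; the stated sensitivity becomes less favourable.

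### The 320 that yields 95% power is also the number randomised; no loss over 18 months is allowed for, and on the two-sided readings that come close to 320 nothing is left to absorb it.

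*Protocol article*

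**What the plan says.** Under Sample size considerations the Protocol article gives its inputs as "Assuming a statistical power of 95% and an effect size of 0.20 regarding continuous outcome measures between intervention and control group" and "with an alpha risk of 0.05". It goes straight to the result: "the sample size is estimated to be 320 participants; that is 80 at each of the four sites with 40 participants in the intervention group". With the matching control group this is 160 per arm. The abstract uses the same figure for enrolment: "A total of 320 participants (80 in each study site and 4 sites in total) will be randomised on a 1:1 basis".

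On follow-up, the Study design section says "A final evaluation will be performed on month 18 (T4"). The statistical analysis section compares the arms at every visit through a treatment-by-time interaction in a multilevel model: "Comparison between the intervention group and the control group at each evaluation moment will be conducted by including an interaction between the treatment groups and" (the second term, cut off here, is time).

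On the population, Table 1 requires age 60 or over and, with some variation by site, severe respiratory disease or multi-morbidity with a condition in a severe stage. The Background says: "Patients with non-cancer chronic conditions may also have significantly impaired HRQoL and poor survival". Outcome data come from self-reported questionnaires.

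The article gives no expected death or dropout rate, no evaluable number and no inflation step. It does not name the effect-size metric or the sidedness of the test, and it does not say to which visit the 95% applies.

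**The concern.** A sample size calculation gives the number of patients with data in the comparison. If that same number is randomised, the stated power needs every patient to contribute at the visit in question. In older patients with mostly severe chronic disease, complete self-reported data from all 320 at month 18 is not credible.

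Month 18 is where observed numbers will be lowest, and it ends the follow-up on which the within-trial cost-effectiveness analysis rests. A null result there would be read as coming from a trial with 95% power. If the true figure is nearer 85 or 90%, the printed one overstates what such a result excludes.

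**Working it through.** **Inputs from the article.** Power 0.95, effect size 0.20, alpha 0.05, 320 in total, 160 per arm, allocation 1:1.

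**Assumptions made here.** Two-sided testing, because sidedness is not stated. Losses of 10–40% by month 18, equal in both arms, because no rate is given. For the mixed model, a correlation of 0.5 between visits.

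**Step 1: reproduce 320.** With z(0.975) + z(0.95) = 1.960 + 1.645 = 3.605:

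- 0.20 as a correlation: N = (3.605 / atanh 0.20)² + 3 = 319.2, so 320.
- 0.20 as Cohen's f, that is d = 0.40: N = 4 × 3.605² / 0.40² = 324.9, or 326 with whole arms; the exact F test gives 327 and the exact t-test 328.
- 0.20 as a standardised mean difference d: N = 4 × 3.605² / 0.20² = 1,299.5, so 1,300.

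The first reading gives 320 exactly and the second comes within 3%. Both consume the whole number. The third does not give 320.

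**Step 2: power at month 18 if 320 are randomised.** n per arm = 160 × (1 − loss). The correlation column uses Φ(atanh 0.20 × √(2n − 3) − 1.96). The two d columns use the two-sample t-test.

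| Assumed loss | n per arm | r = 0.20 | d = 0.40 | d = 0.20 |
|---|---|---|---|---|
| 0% | 160 | 95.0% | 94.6% | 43.0% |
| 10% | 144 | 92.8% | 92.3% | 39.4% |
| 20% | 128 | 89.7% | 89.0% | 35.7% |
| 30% | 112 | 85.4% | 84.6% | 32.0% |
| 40% | 96 | 79.6% | 78.7% | 28.1% |

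Converting r = 0.20 to a difference gives d = 2 × 0.20 / √(1 − 0.04) = 0.408. The t-test then gives 95.4, 93.2, 90.2, 86.0 and 80.3%, the upper end of the ranges quoted.

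**Step 3: what the multilevel model recovers.** Patients lost before month 18 still contribute earlier visits. With visits at 0, 1.5, 6, 12 and 18 months, equal correlations of 0.5 and losses at a constant rate, the effective n per arm for the month 18 contrast is about 149, 138, 126 and 113 at 10, 20, 30 and 40% loss. Power at d = 0.408 is then about 94, 92, 90 and 86%.

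**Step 4: difference detectable with 95% power.** 3.605 × √(2/n) gives:

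- 0.40 SD at 160 per arm
- 0.45 SD at 128
- 0.48 SD at 112
- 0.52 SD at 96

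**Step 5: readings that leave a reserve.**

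- One-sided alpha 0.05 with d = 0.40 needs 272, and 272 / 0.85 = 320, so 15% loss is absorbed exactly. Power is 93.9% at 20% loss and 91.0% at 30%.
- Two-sided d = 0.40 adjusted for baseline at correlation 0.5 needs 326 × (1 − 0.5²) = 244.5, or 246 after rounding up per arm. Power is 95.7% at 20% loss.
- f = 0.20 as a between-group effect averaged over five visits needs 198 at correlation 0.5 and 276 at 0.8. That is an average effect, not a month 18 contrast.

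**The case against.** A reader might infer that the 95% claim cannot hold at month 18 on any reading of the effect size, or that any loss at all takes power below it. The documents do not support either statement. They leave the metric, sidedness and test open, and Step 5 shows readings that keep 95% with real losses. The one-sided case even reproduces 320 as 272 plus exactly 15%. The mixed-model figures in Step 3 also credit no precision for the baseline measurement, which is collected for nearly all patient outcomes. What limits this objection is that each such reading needs something the article does not state: a one-sided test, a correlation, or a baseline-adjusted or repeated-measures calculation.

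It is also fair that the article nowhere calls 320 the evaluable number and nowhere ties the 95% to month 18. Both links are inferred from the arithmetic and from the missing inflation step. The loss rates are assumptions, the Background remark on survival is general, and at 10% loss the gap is only two to three points.

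Finally, a condensed article may leave a dropout rate to the full protocol. That would settle the matter if the article were merely silent. But it prints a power with its inputs and its result, and that result coincides with the number randomised. The printed figure can be checked as it stands, and a reader will rely on it.

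**Conclusion.** The point holds in limited form. The calculated and the randomised number are both 320, and no allowance for loss is stated. On the simple two-sided readings that come close to 320, the number is fully used up. Observed-case power at month 18 is then about 92–93% at 10% loss, 89–90% at 20%, 85–86% at 30% and 79–80% at 40%, with a few points recovered by a mixed model. The shortfall reaches about five points at roughly 20% loss for observed cases and at roughly 30% for the mixed model.

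This rests on assumed losses and two-sided testing, and for the mixed model on a correlation of 0.5. If 0.20 is a standardised mean difference, power is about 43% before any loss. That is a separate effect-size problem; attrition only adds to it and should not be blamed for it.

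**What to change.** Keep 320 as the number randomised. In Sample size considerations:

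1. Name the effect-size metric and the sidedness of the test.
2. State the loss from death and dropout expected by month 18, taken for example from the sites' own records, and the resulting evaluable number per arm. At 20–30% loss this would be 128 to 112 of 160.
3. Replace the single 95% with the power, or the difference detectable with 95% power, at that number for month 18, beside the figure for week 6. At 20–30% loss the detectable difference is about 0.45–0.48 SD, against 0.40 SD with all 160 per arm.

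If 320 already includes an allowance, say so and give the evaluable number from which it was derived; that would settle the point.

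The cost is one recalculation, a few lines of text and probably a less favourable stated power for the 18-month comparison. No extra patients are needed.
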